#### Effectiveness

EBP effectiveness measures will include type of referrals or actions generated by each EBP, and whether they were completed, as measured by EHR template use, administrative consult data, and encounters. We will also use administrative EHR data to measure number of patient encounters with primary care team members (social work, pharmacist, nurse, integrated mental health), as an indicator of engagement of primary care teams for high-risk patient care. Impacts of RIVET on patient experience will be evaluated with a patient survey that includes measures (described above) of satisfaction and access to resources and support for caring for high-risk patients. We will also assess clinical performance metrics that are expected to be directly impacted by each EBP. For both EBPs, we will measure acute care utilization, such as emergency department (ED) visits, total acute and ambulatory care-sensitive (ACS)-related hospitalizations. For MAA, we will also measure adherence to medications for common chronic conditions, such as hypertension and diabetes. See Table 2 for details on included effectiveness measures.

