#### Reach

Reach is defined in this study as the proportion of high-risk patients on each study team’s panel that received one of the EBPs during the 18-month implementation period. See Table 2 for details on included reach measures. We define “high-risk patients” using a VHA-specific risk score called the Care Assessment Need score, previously developed and validated by VA through machine-learning to predict a patient’s risk for a VHA hospitalization or mortality [54]. We define ‘receipt’ as having the EBP assessment at least partially documented in the electronic health record (EHR). We will also examine the patient characteristics (sociodemographic, Elixhauser comorbidity score [66]) of eligible patients who did vs. did not receive the EBP.

**Table 2 Tab2:** Reach and effectiveness outcomes metrics

	**Reach** **(Primary Outcome)**	**Proximal Care Process Impacts**	**Patient and Provider Impacts**	**Clinical Quality and Outcomes**
EBP 1 CACP	Proportion of site-assigned patients in the top 10% of CAN-hospitalization scores that receive the EBP	• Number and type of referrals generated • Referrals completed by patient • Number of primary care social worker, pharmacist, nurse, integrated MH encounters	• Comprehensiveness of Care (Patient Survey^a^/SHEP) • Self-Management Support (Patient Survey^a^/SHEP) • Primary Care provider experience and perceived support for high-risk patient care (Clinician Survey)	• VHA ACS-related and total acute hospitalizations • VHA ACS-related and total emergency department visits
EBP 2 MAA		• Number and type of referrals or actions documented receiving the EBP • Number of primary care pharmacist, social worker, nurse, integrated MH encounters	• Providers Discuss Medication Decisions/Medication Comprehensiveness (Patient Survey^a^/SHEP) • Self-Management Support (Patient Survey^a^/SHEP)	• Medication adherence (Patient Survey^a^) • Adherence for DM, HTN, HL, MH medications (VHA Pharmacy Data) • HEDIS measures for DM, HTN, HL management

*ACS* Ambulatory care-sensitive, *EBP* Evidence-based practice, *CACP* Comprehensive Assessment and Care Planning, *CAN* Care Assessment Need, *DM* diabetes mellitus, *HTN* hypertension, *HEDIS* Healthcare Effectiveness Data and Information Set, *HL* hyperlipidemia, *MAA* Medication Adherence Assessment, *MH* Mental Health, *PDC* proportion of days covered, *SHEP* Survey of Healthcare Experiences of Patients

^a^Refers to patient survey referenced in the Methods

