## Outcomes and data analyses

To analyze our primary outcome, receipt of each EBP among top 10th percentile high-risk patients during the 18-month implementation period (Reach), we will model uptake of both practices in our Concurrent Stepped Wedge Design as a multilevel hierarchical model with a repeated cross-sectional data structure in which sites are followed over time. In this design, the data structure includes patients at level 1 (where Reach, the main outcome of interest, in measured), nested within time at level 2, and nested within sites at level 3. The main predictors will be site implementation strategy assignment (EBQI-IC vs. EBQI-LC vs Usual Care) over time (measure as the number of quarter). We will first describe differences in trends using unadjusted analyses, then add covariates for patient characteristics (i.e., age, sex, Elixhauser comorbidity score [66]) and site-level covariates (i.e., number of unique patients served in primary care, rural vs urban). Secondary analyses of Reach will include models by key patient subgroups, including those hospitalized in the 90 days prior to the quarter examined, and models with an interaction term for assigned implementation strategy by EBQI fidelity level (as defined above), to examine how implementation strategy fidelity may have impacted Reach.

To analyze our secondary outcomes of care processes, patient experiences, provider experiences, and performance measures (Effectiveness), we will first model unadjusted trends in outcomes over time for each EBP, by site implementation strategy assignment. We will then model outcomes using two or three-level (depending on whether the metric is measured at the patient or site level) hierarchical models based on the concurrent Stepped Wedge Design using repeated cross-sectional data, adjusted for the same covariates included in the models for our primary outcome. In models of medication adherence, we will add covariates for medication regimen complexity, as indicated by total number of classes of medication prescribed for the condition of interest, and patient co-pay status. If we find differences in outcomes, we will perform mediation analyses that consider how Reach and EBP fidelity may have mediated outcomes [67].

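### Referrals counted as EBP-generated are about zero in usual care by definition, so their usual-care contrast restates Reach and cannot show whether referral practice changed

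*Protocol article*

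**What the plan says.** - **Definition and data sources.** The Effectiveness section of the protocol article takes as an outcome the "type of referrals or actions generated by each EBP, and whether they were completed, as measured by EHR template use, administrative consult data, and encounters". The sentence covers both EBPs, Comprehensive Assessment and Care Planning (CACP) and Medication Adherence Assessment (MAA).
- **Table 2, proximal care-process column.** The MAA cell reads "Number and type of referrals or actions documented receiving the EBP". The CACP cell reads "Number and type of referrals generated" and adds referrals completed, with no mention of receipt. For both EBPs the column also lists encounters with social work, pharmacist, nurse and integrated mental health staff.
- **Receipt.** Under Reach, a patient has received the EBP if its assessment is at least partly recorded in the electronic health record. The Reach denominator is broad: "Proportion of site-assigned patients in the top 10% of CAN-hospitalization scores that receive the EBP".
- **Analysis.** Outcomes and data analyses names care processes among the secondary outcomes. It first describes trends by assigned strategy, then fits "hierarchical models based on the concurrent Stepped Wedge Design using repeated cross-sectional data". The patients who enter these models are not specified for the referral outcome.
- **Comparator.** Site selection and eligibility makes the periods without active implementation the usual-care periods.

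**The concern.** A stepped-wedge contrast is informative only if the outcome can be observed on the same terms before and during implementation. A referral that counts only because the EBP generated it cannot occur where the EBP is not in use. Usual care then scores about zero whatever clinicians were doing, and the implementation effect on this outcome is positive as soon as anyone uses the EBP and refers. It would be reported as a change in care when it mainly says that the EBP was used, which the primary outcome already measures.

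A second problem depends on a choice that the article does not state. Receipt follows randomisation and may differ between individual consultation (IC) and learning collaborative (LC) sites, both in how many patients are assessed and in which ones. If referrals were analysed per recipient, randomisation would no longer protect the IC-LC comparison.

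At stake is the reading of one part of the Effectiveness results: whether referral practice for high-risk patients changed, and under which strategy it changed more.

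**Working it through.** The article gives no reach, referral rate or target effect, so there is no figure of its own to reproduce. All values below are assumptions for illustration.

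**Notation.** R is reach, the share of eligible patients who receive the EBP. m is EBP-generated referrals per recipient. b is background referrals per eligible patient in usual care, taken as equal for later recipients and non-recipients.

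**1. The usual-care contrast.** EBP-generated referrals per eligible patient are R x m during implementation and about 0 in usual care. The contrast is R x m - 0 = R x m. It does not contain b, so the outcome carries no information about prior referral practice.

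**2. What the contrast should be.** If EBP referrals come on top of background, the true change is also R x m. If they replace background referrals in recipients, the all-source rate is R x m + (1 - R) x b and the true change is R x (m - b). With s = b/m as the share that would have been ordered anyway, the overstatement factor is m/(m - b) = 1/(1 - s). At s = 0.1 this is 1/0.9 = 1.11, and at s = 0.5 it is 1/0.5 = 2. The outcome as defined cannot tell these two situations apart.

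With R = 0.40 and m = 1.0 for IC, and R = 0.20 and m = 1.5 for LC, the EBP-generated contrast with usual care is 0.40 and 0.30 in every row. Under replacement:

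| b (usual care) | IC all-source | IC true change | LC all-source | LC true change |
|---|---|---|---|---|
| 0 | 0.40 | 0.40 | 0.30 | 0.30 |
| 0.3 | 0.58 | 0.28 | 0.54 | 0.24 |
| 0.6 | 0.76 | 0.16 | 0.78 | 0.18 |
| 0.9 | 0.94 | 0.04 | 1.02 | 0.12 |

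The order of the strategies changes where 0.40 + 0.60b = 0.30 + 0.80b, that is at b = 0.5. So replacement can alter even the IC-LC ranking when the denominator is all eligible patients.

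**3. The recipient denominator, if it were used.** Per recipient the comparison is m for IC against m for LC; per eligible patient it is R x m against R x m. When LC has the higher m, the two orders differ only if R(IC)/R(LC) exceeds m(LC)/m(IC). The mirror condition applies when IC has the higher m.

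| R, IC vs LC | m, IC vs LC | Reach ratio vs m ratio | Per eligible, IC vs LC | Order differs? |
|---|---|---|---|---|
| 40% vs 20% | 1.0 vs 1.5 | 2.0 vs 1.5 | 0.40 vs 0.30 | Yes |
| 40% vs 30% | 1.0 vs 1.5 | 1.33 vs 1.5 | 0.40 vs 0.45 | No |
| 40% vs 20% | 1.0 vs 2.5 | 2.0 vs 2.5 | 0.40 vs 0.50 | No |
| 40% vs 40% | 1.0 vs 1.5 | 1.0 vs 1.5 | 0.40 vs 0.60 | No |

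On a grid with R from 10% to 60% in steps of 10 points and m of 0.5, 1, 1.5 and 2, the orders differ in 78 of 408 non-tied combinations (78/408 = 19%). That is a share of an arbitrary grid and not a probability for this trial.

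**The case against.** A reader might infer that these outcomes are counted only from template encounters, that they describe recipients alone, and that they can therefore reverse the IC-LC ranking on care processes. The article does not support that much, for four reasons.

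- Consult and encounter data are named beside the template, and the CACP cell of Table 2 has no restriction to recipients.
- Limiting the numerator to EBP-generated referrals does not set the denominator. The models use the same design as Reach, so all eligible high-risk patients is at least as natural a reading. On that reading the reversal in step 3 does not arise. An article may leave the analysis set of a secondary outcome to a fuller document.
- Care processes also include the team-member encounter counts, which come from administrative data and are not tied to receipt.
- The reversal needs assumed rates. If s is the same under both strategies, 1/(1 - s) leaves the IC-to-LC ratio unchanged.

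All of this stands. It does not reach the usual-care problem. In the Effectiveness text the consult and encounter data serve to measure EBP-generated referrals, for both EBPs. A later analysis plan can supply a denominator, but it cannot make a numerator tied to the EBP comparable with periods that lack the EBP unless it changes the printed outcome. The encounter counts do not capture referral type, referral completion or MAA actions.

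A consult-only replacement would also lose MAA actions such as coaching during the assessment, which need not lead to a consult. That objection is right, and the fix keeps them.

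**Conclusion.** The concern holds for the referral and action outcome in its contrast with usual care. The comparator is about zero by definition, so the contrast reports reach times referrals per recipient and cannot show a change in referral practice. The size of the error depends on how many EBP referrals replace ones that would have been made anyway: none if they are all additional, 11% at one in ten, 100% at one in two. The article gives no basis for choosing among these.

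The IC-LC part is conditional. Conditioning on receipt arises only if the analysis is per recipient, which is not stated, and a different ranking then needs the reach ratio to outweigh an opposite ratio of referrals per recipient. Replacement can also change the ranking per eligible patient, again only at certain assumed rates.

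The scope is one component of a secondary domain. Reach keeps its full eligible denominator, and the team-member encounter counts are untouched. The change should still be made, because it is cheap and without it the outcome cannot answer the question put to it.

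**What to change.** For both EBPs, define the modelled referral outcome as the number of all relevant consults, and their completion, per eligible high-risk patient per quarter. Relevant consults are those to social work, pharmacy, nursing, integrated mental health and the other referral types on the templates. Take them from administrative consult data in every site and every period, usual care included, whether or not the EBP was used. Bring the Effectiveness text and both Table 2 cells into line with this and state the denominator.

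Keep EBP-generated referrals, and MAA actions that produce no consult, as measures of EBP content. Report them descriptively among recipients, or per eligible patient for IC versus LC only. In neither form should they be contrasted with usual care.

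The cost is a wording change and a wider extract from a source that the article already names. Background consults will add noise, and the apparent effect per patient will be smaller than an EBP-generated count would show.

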### Evidence‑based practices (EBPs)

We selected two EBPs that guide primary care teams to identify modifiable needs among high-risk patients through standardized assessments and utilize the expertise of the multidisciplinary staff in the primary care team: Comprehensive Assessment and Care Plan (CACP) and Medication Adherence Assessment (MAA).

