#### EBP Comprehensive Assessment and Care Plan (CACP) for high-risk patients

The CACP is an assessment that helps the primary care team to develop an individualized treatment plan based on identified needs for high-risk patients of any age [35]. It was adapted from the Comprehensive Geriatric Assessment (CGA), which has been shown in multiple randomized control trials (RCTs) to lead to improved outcomes for older adults with complex care needs [36, 37]. According to meta-analyses, the CGA has consistently led to improved outcomes for frail, older adults, such as decreased mortality (OR 0.86, 95% CI 0.75–0.98), decreased readmissions (OR 0.88, 95% CI 0.79–0.98), and decreased length of stay (1.63–40.7 days in intervention group vs 1.8–42.8 days in usual care) compared to those who did not receive the CGA [38–40].

While the CGA assesses several domains that are important for complex patients, some domains may not be broadly applicable to high-risk Veterans of all ages (i.e., nutrition, vision, hearing, continence). According to our analyses, half of high-risk Veterans are younger than 65 years old and have greater psychiatric comorbidities than older high-risk Veterans [6]. We added domains to specifically assess for modifiable risk factors that are common among high-risk Veterans (e.g., transportation assistance, health literacy, behavioral health symptoms, and coordination with non-VHA healthcare systems) [41–43]. The CACP screening questions are taken from standard sources, including the National Academy of Medicine Recommendations for High-Need Patients [44] and the Protocol for Responding to and Assessing Patients’ Assets, Risks, and Experiences (PRAPARE) [45].

The CACP prompts the primary care team member to explore identified risk factors further or to refer to another team member for an in-depth assessment if needed. After the assessment, the CACP is then used to guide the development and implementation of an individualized treatment plan that addresses the patient’s health-related needs in the context of the patient’s preferences [10]. The treatment plan can be coordinated and monitored through team huddles (consisting of the primary care provider, nurses, clerk) or monthly interdisciplinary team meetings.

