### Setting

VHA primary care uses a multi-disciplinary patient-centered team-based approach (Patient-Aligned Care Teams; PACTs) where teams of health care professionals provide longitudinal care to a panel of patients [35]. Team members include a primary care provider, nurses, clerk, integrated mental health provider, social worker, and a pharmacist. Teams have access to multiple dashboards and reports for care management, including the Care Assessment Need (CAN) score [54], which describes the patient’s risk for future VA hospitalization or death by percentile.

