#### Adoption

We will assess adoption by measuring number and proportion of staff trained on each EBP, and how many and which types of staff delivered each EBP (representativeness), using administrative training records and administrative clinical data for each EBP.

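### The encounter-count outcome can include the visit at which the EBP was delivered, so it cannot separate delivery from added care and can overlap with Reach

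*Protocol article*

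**What the plan says.** The Effectiveness section of the protocol article measures the "number of patient encounters with primary care team members (social work, pharmacist, nurse, integrated mental health), as an indicator of engagement" of the primary care team with high-risk patients. Table 2 lists the same count among the proximal care process impacts of both EBPs: "Number of primary care social worker, pharmacist, nurse, integrated MH encounters" for CACP and "Number of primary care pharmacist, social worker, nurse, integrated MH encounters" for MAA. Neither place separates the encounter at which the EBP was documented from other encounters.

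On who delivers the EBP, the article gives the following:
- Setting: "Team members include a primary care provider, nurses, clerk, integrated mental health provider, social worker, and a pharmacist". The four counted disciplines are on this list. The provider and clerk are on it too but are not counted.
- Evidence-based practices: the EBPs "utilize the expertise of the multidisciplinary staff in the primary care team".
- CACP: "The CACP prompts the primary care team member to explore identified risk factors further or to refer to another team member".
- EBQI activities: which staff might perform the assessment is a matter for discussion with stakeholders.
- Adoption: "how many and which types of staff delivered each EBP" is itself to be measured.

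Receipt of the EBP, which defines Reach, requires at least partial documentation in the health record. Outcomes and data analyses includes care processes among the secondary outcomes and, if differences are found, plans "mediation analyses that consider how Reach and EBP fidelity may have mediated outcomes".

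**The concern.** The count is offered as evidence that the EBP draws the team further into the care of high-risk patients. Suppose a nurse or pharmacist sees a patient only to complete the template and nothing follows. That patient is counted once as reached and once more as having an additional team encounter. A comparison of EBQI with usual care, or of IC with LC, could then show more engagement when the only thing that changed was delivery of the assessment.

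Mediation raises the same difficulty. If receiving the EBP can itself create a unit of the outcome, a finding that Reach explains the difference in encounters is partly true by definition.

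**Working it through.** **Inputs.** The article gives no expected Reach, encounter rate or split of deliverers, so it has no figure to reproduce. All values of Reach, q, s and baseline below are assumptions.

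**Set-up.** Assume one delivery encounter per recipient and no EBP documentation in usual-care periods. Let
- R = Reach,
- s = share of deliveries made by a counted discipline,
- q = share made by a counted discipline at a visit that would not otherwise have occurred (0 ≤ q ≤ s ≤ 1).

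q is zero if the primary care provider always delivers the EBP, or if delivery always falls within a visit that would have taken place anyway.

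**Step 1: all encounters counted.** With no care added after the assessment, the count still rises by R × q per eligible patient:

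| R | q = 0 | q = 0.25 | q = 0.5 | q = 1 |
|---|---|---|---|---|
| 10% | 0 | 0.025 | 0.05 | 0.10 |
| 30% | 0 | 0.075 | 0.15 | 0.30 |
| 50% | 0 | 0.125 | 0.25 | 0.50 |

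At R = 30% and q from 0.25 to 1, this is 0.075/2 = 3.75% to 0.30/2 = 15% of an assumed baseline of 2 encounters. At a baseline of 6 it is 0.075/6 = 1.25% to 0.30/6 = 5%.

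**Step 2: between strategies.** The built-in difference is R_IC × q_IC − R_LC × q_LC. With equal q and a 20-point difference in Reach it is 0.20 × q, that is 0, 0.05, 0.10 or 0.20 for q = 0, 0.25, 0.5 or 1. Equal Reach does not remove it if the deliverers differ: R = 30% in both, with q = 0.75 against 0.25, gives 0.225 − 0.075 = 0.15.

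**Step 3: delivery encounter excluded.** The added visits drop out, but so do delivery visits that would have happened anyway, and usual care loses nothing comparable. The bias is −R × (s − q). With R = 30%, s = 1 and q = 0.5, inclusion gives +0.15 and exclusion −0.15. With s = 1 and q = 0, exclusion gives −0.30 and inclusion is unbiased. The gap between the two versions is R × q + R × (s − q) = R × s, which the trial data will show even though q cannot be observed.

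**Step 4: mediation.** With no downstream effect, and receipt unrelated to other visits, recipients exceed non-recipients by q encounters. With equal q, the path through Reach is then (difference in Reach) × q, which is the whole of the built-in difference in step 2. Reach would appear to explain all of an effect that is not there. On the count without the delivery encounter, the corresponding slope is −(s − q), so that version alone is not neutral either.

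**Step 5: simulation.** Gamma-Poisson counts with no downstream effect (400,000 patients per scenario, baseline 2 or 4, Reach 10% to 50%) gave recipient minus non-recipient differences of about 0 at q = 0, 0.5 at q = 0.5 and 1.0 at q = 1. The patient-level correlation between receipt and count was 0.03 to 0.20 for q = 0.5 to 1, and about 0 for q = 0.

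**The case against.** The strongest reply has four parts.

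1. **The article is condensed.** A counting rule with index dates and same-day exclusions may sit in a fuller document. That is possible, and the absence of such a rule is not the point. The point is that the outcome, as the article defines it and lists it among impacts, cannot tell delivery from added care.

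2. **Being assessed by a nurse or pharmacist is engagement.** This is a fair reading of the stated construct, and the article separately measures referrals or actions and their completion, which shows some of what followed. But a delivery visit is already credited as Reach, so it is not further evidence of an effect.

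3. **Overlap is not certain.** A reader might infer that the counted staff are the ones who deliver the EBP, so that every reached patient adds an encounter, EBQI must look better and the outcome merely re-measures Reach. The article does not support this. It leaves the deliverer open, the provider's encounters are not counted, and receipt requires documentation, not a separate visit. The simulated correlations also show only partial coupling.

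4. **Excluding the delivery visit has its own bias.** This stands in full. Step 3 shows that the opposite error can be just as large, so exclusion should not become the sole main definition.

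The mediation is also conditional on differences being found, and it is described for the secondary outcomes together. That limits how often the circularity will matter, but does not remove it.

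**Conclusion.** The point holds in a limited form. The count takes in encounters with staff who may deliver the EBP, so a delivery made by one of them at an added visit can score as an effect. The built-in part is Reach × q encounters per eligible patient. It is zero when q = 0 and at most equal to Reach. Its actual size cannot be derived from the document; the figures above show only a range under assumed values, with one delivery encounter per recipient.

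The planned mediation by Reach is partly circular for this one outcome when q exceeds zero. The primary outcome is unaffected, and nothing here bears on the other effectiveness measures. Because this is one secondary process measure and the remedy is cheap, it is worth correcting but does not threaten the trial's main comparison.

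**What to change.** - Report the encounter count with and without the encounter at which the EBP template was documented. The health-factor data described under EHR Administrative data should allow that encounter to be identified.
- Treat the two versions as bounds: inclusion can overstate the effect by Reach × q, and exclusion can understate it by Reach × (s − q).
- Claim added engagement beyond EBP delivery only if both versions agree.
- Run any mediation by Reach on both versions, or on encounters after the EBP with a matching index date for non-recipients and usual-care periods. Do not run it on the all-encounter count alone.

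The cost is a little extra analysis of data already planned for extraction, with no new collection. The price is a less definite reading if the two versions disagree.
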